**Figure 4 figure4:**
[figure not shown]
Participant options for genetic testing. eREACH: A Randomized Study of an eHealth Delivery Alternative for Cancer Genetic Testing for Hereditary Predisposition in Metastatic Breast, Ovarian, Prostate, and Pancreatic Cancer Patients.

#### Disclosure of Results (Visit 2)

Those randomized to genetic counseling for visit 2 (arms A and C) are contacted via phone by their assigned GC to share their results. These are not scheduled calls, and GCs make up to 5 attempts over 10 days (routine cases) and up to 3 attempts over 3 days (urgent cases). For the disclosure sessions, a visual aid packet that is publicly available for clinical use, is provided to all participants, GCs complete disclosure checklists, and all sessions are recorded unless participants decline.

Those randomized to the digital intervention for visit 2 (arms B and D) are provided with their result and gene-specific screens (as appropriate), which are first reviewed by 2 study team members (a research team member and the GC) for accuracy and quality control. Results are uploaded into the digital intervention by a study team member. Participants are notified via email that results are available and can be accessed and that they can request to speak with a GC if they prefer before or after viewing their results. After return of results, the GC provides the referring or registered health care provider with the genetic test results and chart note. GCs are available to answer any patient or health care provider questions. Study team members contact patients via email or phone up to 5 times every 2 to 3 days for those who have not accessed the digital intervention after their results have been released. If results are not viewed after these reminders, the participants are contacted by their assigned GC to attempt to disclose results. If this is unsuccessful, a notification is sent to the treating physician to make them aware, and the results are provided to the treating physician. As of September 2023, all results have been also uploaded to the electronic medical record in accordance with Penn Medicine’s policies to comply with the 21st Century Cures Act.

### Outcomes

#### Uptake of Testing and Patient-Reported Outcomes (Aim 1)

Theoretically informed patient-reported cognitive, affective, and behavioral outcomes of genetic services will be collected at baseline (T0), after visit 1 (T1) and visit 2 (T2), and at 6 months (T3).

Uptake of counseling and testing is assessed through Penn Telegenetics service records for those assigned to (or who select) standard-of-care genetic counseling. Uptake for those assigned to the digital intervention will be recorded as completion of the digital intervention.

Understanding of genetic information is assessed at all time points (T0-T3). Knowledge of genetic disease will be evaluated using The KnowGene Scale, a 16-item scale administered to patients after genetic counseling and testing to measure their understanding of the health implications of genetic test results. It includes health implications to oneself as well as relatives and covers penetrance, actionability, limitations of current technology, and monogenic inheritance patterns [49].

Reactions to genetic information are assessed using multiple instruments that evaluate psychological distress, adjustment, and satisfaction:

General anxiety and depression are assessed using the 4-item short Patient-Reported Outcomes Measurement Information System [50,51].Disease-specific distress is measured using the 8-item Impact of Event Scale [52-55], which has strong internal consistency (Cronbach α=0.82-0.90) in genetic delivery studies [56-58].Satisfaction with genetic services is assessed using 14 items evaluating satisfaction with genetic services (T1 and T2). These items have been used in our related studies evaluating alternative and traditional genetic testing delivery models (Cronbach α=0.73-0.85) and adapted for digital delivery [17,56,57,59-62].Multidimensional responses to genetic testing, including positive responses and uncertainty, will be assessed using the Multidimensional Impact of Cancer Risk Assessment questionnaire at T2 and T3. The Multidimensional Impact of Cancer Risk Assessment questionnaire has been used in many genetic studies to evaluate distress, uncertainty, and positive responses to receipt of genetic test results [63]. Four items were excluded as they were not relevant to patients with metastatic cancer.Decisional regret (T2 and T3 only) is assessed using the 5-item validated Decision Regret Scale used frequently in related genetic studies [64,65].

Use of genomic information includes change in treatment plan and communication of results (T3) to health care providers, family members, and others using items adapted from our related studies. For all actionable results (*BRCA1* and *BRCA2* and Lynch syndrome genes), we either confirm changes in the treatment plan in the medical record (Penn Medicine patient and health care provider participants) or by contacting the treating oncologist for confirmation of whether the patient received a PARP inhibitor or immunotherapy and, if not, why.

Health care provider time is recorded per patient for a subset of participants to estimate health care provider time by arm. This includes time for remote telehealth counseling. For patients in arms B to D, where services have the potential to be completed partially or entirely by the digital intervention, these patients will still have a GC review their history, decision, and support testing submission; review results and the disclosure information provided; and be available for questions upon request. Thus, in all arms, GC time for case review, genetic counseling, and conversations with patients and their health care providers will be recorded for a subset of patients.

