### Objectives

#### Overview

The goal of the eREACH study is to evaluate the effectiveness of replacing traditional pretest (visit 1—education and consent) and posttest (visit 2—disclosure) counseling delivered by a GC with an interactive patient-centered digital intervention for germline genetic testing in patients with advanced or metastatic cancers for which a PARP inhibitor could be considered for treatment. We hypothesize that offering digital alternatives for pretest or posttest (result disclosure) visits will result in equal or improved (noninferior) short-term and longitudinal cognitive, affective, and behavioral outcomes and reduce health care provider time, increasing throughput and access to genetic services. Furthermore, we will evaluate subgroups who benefit more or less from digital alternatives, which will provide critical information on how best to implement and increase access to germline genetic testing in the era of precision medicine.

#### Specific Aim 1

Our primary aim is to determine whether a patient-centered digital intervention delivery of pretest or posttest counseling can yield equal or improved short-term cognitive and affective outcomes as compared to a 2-visit telehealth delivery model with a GC. Our primary outcomes are change in knowledge and general anxiety from baseline to postdisclosure assessment. Secondary outcomes include uptake of testing, depression, cancer-specific distress, uncertainty, change in treatment plan, communication of results, and health care provider time.

#### Specific Aim 2

Our secondary aim is to evaluate patient and delivery factors that moderate the impact of digital delivery alternatives on short-term and longitudinal cognitive, affective, and behavioral outcomes and health care provider time.

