### Study Design

eREACH is a noninferiority study using a 2 × 2 design where traditional standard-of-care pretest (visit 1—education and consent) or posttest (visit 2—disclosure) counseling delivered by a GC are replaced with a patient-centered digital intervention (Figure 1). All patients randomized to the digital intervention can request to speak with a GC instead of completing the digital intervention or at any time during the process.

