### Patient-Centered eHealth Intervention

The patient-centered digital intervention is informed by the tiered-binned model and designed to replace a traditional counseling session for patients who find this to be sufficient information. The intervention includes tier 1 (indispensable information presented to all users) and optional tier 2 content (more in-depth information, examples, and videos). Completing tier 1 takes 11.5 to 14 minutes for the average user, and it takes 28 minutes to review all content and videos. Readability testing was completed for all content, and modifications were made to achieve a readability score of eighth grade or lower when possible. As shown in Table 1, the pretest intervention includes eight modules: (1) introduction, (2) purpose of testing, (3) genetics overview, (4) implications of results, (5) possible results and implications, (6) genetic testing options, (7) things to consider before genetic testing, and (8) testing decision. Example screenshots are shown in Figure 2.

After viewing the minimum tier 1 screens, participants are asked to record their decision to either proceed with testing and their testing choice (targeted test only, gene panel testing, or large or custom panel testing) *or* decline testing and their reason. Those who log a decision to move forward with testing have their selection, along with the details of their personal and family history, reviewed by a study GC. In the event that a study GC feels that an alternative decision for testing may be more appropriate based on family history, patients will receive a call and speak with the GC to confirm their decision.

The patient-centered digital result disclosure (visit 2) intervention includes four modules: (1) welcome page and instructions, (2) test result, (3) explanation of result, and (4) next steps (Table 2). Completing tier 1 once takes approximately 4 to 5 minutes for the average user, and it takes approximately 9 to 10 minutes to review all content and videos. Readability testing was completed for all content, and modifications were made to achieve a readability score of eighth grade or lower when possible. Example screenshots are shown in Figure 3.

**Table 1 table1:** eREACH (A Randomized Study of an eHealth Delivery Alternative for Cancer Genetic Testing for Hereditary Predisposition in Metastatic Breast, Ovarian, Prostate, and Pancreatic Cancer Patients) patient-centered eHealth pretest education (visit 1) intervention.

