#### Genetic Testing

In all study arms, there are 3 available options for testing (Figure 4). Option 1 is a targeted panel limited to genes that could immediately impact treatment for metastatic cancer (*BRCA1* and *BRCA2* and Lynch syndrome). Additional homologous recombination repair genes will be tested for patients with prostate cancer based on the Food and Drug Administration label for the use of PARP inhibitors in this tumor type. Option 2 is a larger gene panel including additional genes related to their cancer type that could have an impact on treatment in the future or additional impact for relatives. Option 3 is a customized panel based on other health concerns or a desire to exclude particular genes. For option 3, participants are asked to speak with a GC to review their concerns and options. Those who log a decision on the digital intervention (arms C and D) have their selection, along with the details of their personal and family history, reviewed by their assigned study GC. In the event that the GC feels that an alternative decision for testing may be more appropriate (ie, the participant selects the targeted panel when a large or custom panel may be indicated), the GC calls the participant to confirm their decision. Self-referred participants are asked to provide contact information for an oncologist (or other health care provider) to serve as the ordering health care provider with the GC as required by state licensure laws. The Penn Telegenetics clinical team contacts the health care provider’s office to give them information about the program and procedures and confirm the health care provider’s information to include in the testing order.

Consistent with current clinical care, all genetic testing will be sent to a commercial laboratory (eg, Invitae or Ambry Genetics) and covered by insurance. At the time, laboratories would notify patients if out-of-pocket expenses of >US $100 were expected. Patients are instructed to contact the GC for any questions regarding coverage and cost. Test kits are sent to the participants’ home, and participants receive as many as 3 reminders to return their test kits. When requested, patients can have their samples collected at the University of Pennsylvania phlebotomy laboratory.

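### Uptake of testing, a secondary outcome, is not counted by the same event in all arms: service records for counselor delivery, module completion for digital delivery

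*Protocol article*

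**What the plan says.** All references are to the protocol article.

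- **The outcome.** Specific Aim 1 states: "Secondary outcomes include uptake of testing". Expected Findings predicts that uptake of genetic testing in the digital arms will match or exceed that under standard of care.
- **Counselor rule.** Uptake of Testing and Patient-Reported Outcomes (Aim 1) states: "Uptake of counseling and testing is assessed through Penn Telegenetics service records for those assigned to (or who select) standard-of-care genetic counseling".
- **Digital rule.** The next sentence reads: "Uptake for those assigned to the digital intervention will be recorded as completion of the digital intervention".
- **End of the visit 1 module.** Patient-Centered eHealth Intervention states: "After viewing the minimum tier 1 screens, participants are asked to record their decision to either proceed with testing and their testing choice". The alternative is to "decline testing and their reason".
- **After the decision.** Genetic Testing adds counselor review of the selection, and then: "Test kits are sent to the participants’ home, and participants receive as many as 3 reminders to return their test kits".
- **Switching.** Study Design states: "All patients randomized to the digital intervention can request to speak with a GC instead of completing the digital intervention or at any time".
- **Visit 2.** Under Disclosure of Results (Visit 2), arms B and D see their own result in the module. They may ask for a counselor. If the module stays unopened after reminders, a counselor tries to disclose and, failing that, the result goes to the treating physician.

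**The concern.** The outcome is named as uptake of testing, and the two adjacent rules count different events. One is tied to counseling and testing in service records. The other is tied to finishing a web module, with no link to a test. A participant can finish the visit 1 module without being tested, and a participant can be tested without finishing the visit 2 module.

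At stake is the comparison announced in Expected Findings. If uptake in the digital arms is reported as equal to or better than standard of care, the reader must know that the same event was counted in each arm. As written, part of any difference, or of any apparent similarity, could come from the counting rule.

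**Working it through.** The article gives no uptake rate, margin or power for uptake, so there is no figure to reproduce. The check sets the rules against the participant pathway.

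**Step 1. Which rule applies in which arm**

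| Arm | Visit 1 | Visit 2 | Rule that applies |
|---|---|---|---|
| A | counselor | counselor | service records |
| B | counselor | digital | both; digital criterion can only be visit 2 |
| C | digital | counselor | both; digital criterion can only be visit 1 |
| D | digital | digital | digital; visit 1, visit 2 or both not stated |

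**Step 2. Module completion against being tested**

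Let t be the proportion tested, c1 the proportion completing the visit 1 module and c2 the proportion completing the visit 2 module. Then:

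- Visit 1 criterion: c1 − t = P(completed, not tested) − P(tested, module not completed). The first term holds those who decline at the end of the module or do not return the kit. The second holds those who use a counselor instead and are tested. The sign is not fixed.
- Visit 2 criterion: c2 − t = −P(tested, module not completed). The module shows the participant's own result, so nobody can complete it untested. The error can only be zero or downward.

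So arm C, and arm D on a visit 1 reading, can be overstated or understated. Arm B, and arm D on a reading that requires visit 2, can only be understated.

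**Step 3. Participants who switch**

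A digital-assigned participant who asks for a counselor and is tested comes under service records through the words in parentheses in the first sentence. The second sentence classes the same person by assignment, as not having completed the module. The article does not say which sentence prevails.

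**Step 4. Illustration only (assumed rates)**

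Assume equal true testing uptake in arms A and C (70% or 80%), arm C scored by visit 1 completion, and completion 5, 10 or 15 points above testing. Take n = 60 per arm, the revised goal in Enrollment Goals. That goal counts participants with baseline and post-disclosure data, so the number available for uptake may differ. For a two-sided 0.05 test of two proportions, also assumed:

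P(reject) ≈ Φ{[Δ − 1.96·√(2p̄(1−p̄)/n)] / √[(p1(1−p1) + p2(1−p2))/n]}

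Example, 80% against 90%: p̄ = 0.85; √(2 × 0.85 × 0.15/60) = 0.0652; √((0.16 + 0.09)/60) = 0.0645; (0.10 − 1.96 × 0.0652)/0.0645 = −0.43; Φ = 0.33.

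| False gap | True uptake 70% | True uptake 80% |
|---|---|---|
| 5 points | 0.09 | 0.11 |
| 10 points | 0.24 | 0.33 |
| 15 points | 0.50 | 0.71 |

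The gap is an input, not a finding. The table shows only how often a given gap would pass for a real effect.

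**The case against.** **The second sentence may be only the digital counterpart of attending counseling.** It says uptake, without testing, so session completed could be set against module completed, which is like with like. This is a fair reading. But then no rule for uptake of testing exists for digital-assigned participants, and the outcome named in Specific Aim 1 is still not measured in the same way across arms. It is also not a detail left to a fuller document: the article does state a rule, and that rule does not match the named outcome.

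**Visit 2 completion implies a test.** This stands. A reader might infer that uptake is inflated in the digital arms as a group. The documents do not support that. Inflation is possible only where visit 1 completion is the criterion; on a visit 2 criterion the rule is stricter than being tested.

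**Those who switch are already covered.** Partly. The first sentence sends them to service records, but the second still classes them by assignment. The Moderator Analysis section promises intention-to-treat, per-protocol and as-treated groupings. That settles how people are grouped, not which event is counted.

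**The conclusion does not rest on uptake.** This stands. Noninferiority is judged on change in knowledge and anxiety. Uptake is one of several secondary outcomes, and its place first in the list implies no ranking.

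**Conclusion.** The point holds for the definition of one secondary outcome. As written, uptake of testing is counted by different events across arms, the qualifying visit is not stated for digital delivery, and a digital-assigned participant who chooses a counselor falls under both rules.

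Neither the direction nor the size of the resulting bias can be determined from the documents: they give no rate of declining, of kit non-return, of switching or of disclosure outside the module. The probabilities in the illustration depend wholly on the assumed gap and should not be quoted as the size of the problem.

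A reader might go further and infer that the trial's main conclusion, or its case for wider access, is compromised. The documents do not support that. The co-primary analyses do not use uptake, and the objectives tie throughput and access to provider time as well.

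**What to change.** Define uptake of testing by one test-based event in all four arms, analysed by randomised arm, for example a germline test completed with a result issued, taken from service or laboratory records. Sample received or test ordered would also serve, provided the same event is used everywhere. A participant assigned to digital who is tested through a counselor then counts as tested in the assigned arm.

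Report separately, by randomised arm, completion of pretest education by any mode and completion of disclosure by any mode. Keep module completion as the adherence measure already defined under Moderators of Uptake and Patient-Reported Outcomes (Aim 2), which is all of tier 1 at least once.

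The cost is a sentence or two and, as far as the article shows, no new data collection: a counselor supports test submission in arms B to D, kit return is followed with reminders, and results pass through the study team. The Results section says that data collection is complete and analysis is ongoing, so the definition should be dated, with a statement of whether uptake by arm had already been seen.

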#### Moderators of Uptake and Patient-Reported Outcomes (Aim 2)

Moderators are collected at baseline and include the following:

Sociodemographic data, including race and ethnicity, educational level, marital status, sex, and age.Health literacy—assessed using 3 Brief Health Literacy Screen items that have been validated to detect inadequate health literacy in clinical medical populations [66].Comfort with technology—assessed using 8 selected Health Information National Trends Survey items [67].Psychological impacts due to the COVID-19 pandemic—assessed in a subset of patients (start of recruitment until May 2023) using the Social Psychological Measurements of COVID-19: Coronavirus Perceived Threat, Government response, Impacts, and Experiences Questionnaires, a 14-item measure previously published by the University of Montana in April 2020. While this protocol is independent of COVID-19, it was advised to use a measure that may help assess for psychological distress that is due to the COVID-19 pandemic separate or in addition to any psychological impacts from receiving genetic testing results [68].

In addition, individual use of the digital intervention is recorded throughout the study to evaluate the impact of intervention use (eg, dosage) on outcomes and who benefits more and less from the intervention. Intervention use includes actual use, adherence, and attrition [69,70]. For actual use, we record the time when each participant logs in and logs out. Actual use will be evaluated for the intervention in general and secondarily for specific intervention content (eg, videos and specific pages). Adherence will be defined as completing all of tier 1 at least once.

### Data Analysis Plan

#### Primary Noninferiority Analysis

We hypothesize that the intervention arms incorporating the digital delivery intervention, with access to a GC upon request, can yield equal or improved short-term and longitudinal cognitive, affective, and behavioral outcomes and lower health care provider time. Our primary outcomes are change between T0 and T2 in knowledge and anxiety. We will test whether the digital intervention is noninferior to standard-of-care counseling with a GC. In noninferiority tests, the null and alternative hypotheses are the reverse of the usual; in this case, the null hypothesis is that the web intervention is worse than the standard of care. We will conclude that the web intervention is noninferior using a modified noninferiority ANOVA of the T2 minus T0 change scores. More details on the power and type I error are provided in the following section. We will use an intention-to-treat approach comparing randomization arms, but we will also confirm results in secondary per-protocol analyses; many recommend that both intention-to-treat and per-protocol analyses be consistent to declare noninferiority [71]. In secondary analyses, we will test pairwise differences among the 4 groups. For longitudinal analyses across the 3 survey times (T0-T3), we will examine time trajectories using regressions estimated through generalized estimating equations to account for within-subject correlation over time. We will include main and interaction terms of arm with time panel indicators.

Our noninferiority test will be based on an ANOVA *F* statistic test jointly comparing the 4 randomization arms, in which we declare noninferiority if the joint *P* value is of >.15 and all 3 experimental web arms have an observed standardized effect of −0.25 SD units or better (with the direction standardized such that higher values imply more beneficial change) when compared to the control standard of care–only arm. If the ANOVA *F* test *P* value is ≤.15, then we will declare noninferiority if the 3 standardized one-sided 85% confidence bounds for the 3 intervention arms relative to the controls are >−0.35 SDs. We define standardization as rescaling variables to have an SD of 1 relative to the pooled baseline SD (see more details in the following section).

#### Sample Size Justification for Aim 1

We originally anticipated 140 participants per arm (560 in total). We chose our 2 primary variables as they demonstrated possible differences between groups in preliminary data from a prior study in which genetic test results were returned to patients; in this study, we expect that harmful changes will not occur. We will use a noninferiority test and, to be conservative, will require noninferiority in both the intention-to-treat and per-protocol analyses, as recommended [71].

With 140 people per arm, we have <1% noninferiority type I error and >82% noninferiority power if we simply use the first criteria that the *P* value must be >.15 and all 3 intervention arm coefficients must be >−0.25 (ie, in the direction away from being harmful when compared to the standard-of-care group). If we further apply the decision rule that the 85% one-sided CIs are bounded away from −0.35 if *P*≤.15, the power increases to 94%, and the type I error rate remains at <1%.

In calculating the type I error rate, we assumed that the 4–change score standardized means (standardized to have an SD of 1) for the null hypothesis were 0 (arm A=control group), 0.3 (single web intervention arms), and −0.6 (double web intervention arm), with negative values indicating a harmful effect. Our alternative hypothesis was a null effect (4–change score means of 0). These were conservative estimates of changes based on standardized RESPECT web intervention findings of a change score movement of 0.3 in anxiety and a change score movement of 0.4 in knowledge. Hence, we have excellent noninferiority power. Calculations were made using PASS (version 11; NCSS Statistical Software) in conjunction with R simulations (R Foundation for Statistical Computing). In secondary analyses, we will examine pairwise comparisons among the 4 arms using 2-tailed *t* tests.

In Multimedia Appendix 1, we provide the probability of declaring noninferiority under a range of assumptions about the intervention effects relative to the standard-of-care control arm. We see that our probability of declaring noninferiority is appropriate under several assumptions about population-level mean differences among arms.

On the basis of low recruitment, we conducted an unplanned conditional power calculation (December 1, 2023) using data recorded until October 24, 2023, to determine whether it would be appropriate to end recruitment at 60 participants per arm. The statistician and the principal investigator were unblinded to the analysis, but the rest of the staff and coinvestigators were blinded. We used the same decision rules for declaring noninferiority as mentioned previously. We present the findings in Table 5. In the “Original assumptions” section, we replicated the findings of the original power calculations (Multimedia Appendix 1) but, instead, assumed a sample size of 60 participants per arm. In the “Genetic knowledge” and “PROMIS anxiety” sections, we conditioned on the probability of declaring the study noninferior on the observed data from the first participants enrolled through October 2023. Next, we simulated data for the future participants based on the assumptions in each row. We added the simulated data to the observed data and tested our noninferiority hypothesis. We iterated the simulations 50,000 times, creating simulated future participant data each time, and calculated the proportion of iterations in which we would conclude noninferiority. Conditioning on the data obtained until October 24, 2023, we have excellent power under assumptions of no effect or beneficial effects or an assumption that the future data will have the same average responses as the data collected until October 24, 2023. For anxiety, the noninferiority type I error rate (ie, the probability of declaring the study noninferior if the intervention is harmful) is still relatively low, which is appropriate.

Regarding standardization, we will standardize the change scores with respect to the baseline SD among the 4 groups (ie, before patients have received any component of the intervention). Hence, our power calculations assume change score SDs of 1, which would be the case if the within-person correlation of measurement between periods is 0.5 (SD of change score = 1 + 1 − 2 × 0.5 × 1 = 1). If the correlation is of >0.5, as may likely be the case, the power will be better.

Regarding the choice of −0.25 as a lower noninferiority bound, we chose −0.25 as an absolute 0.25 standardized effect is often considered a small effect. Hence, our noninferiority margin only tolerates small negative effects. If the *P* value is of ≤.15, we nonetheless ensure that the bound of the one-sided CI is >–0.35, which is still of modest magnitude.

Regarding the choice of our alternative hypothesis, it assumes that all average change scores are 0 (4 mean changes of 0). This is conservative as it does not assume any benefit of the interventions when compared to arm A (the control group). If the web intervention does have a beneficial effect, the power for the noninferiority design will be even better, as shown in Multimedia Appendix 1 and Table 5.

**Table 5 table5:** Probability of declaring the study noninferior under various assumptions about standardized change score means (N=60 per arm; SD 1 for all mean values).

General assumption		Arm A (control), mean (SD)	Arm B (web visit 2), mean (SD)	Arm C (web visit 1), mean (SD)	Arm D (web visits 1 and 2), mean (SD)	Probability of declaring the study noninferior (%)

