### Study Arms

#### Overview

Once participants have completed informed consent, the baseline (T0) survey, and family history collection with research staff, they are randomized into 1 of the 4 study arms. Randomization is stratified by sex and cancer type using a permuted block design within strata for randomization. The allocation sequence was generated by the study biostatistician and made available to research staff.

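### The primary test, an arm-only ANOVA of change scores, is valid but inefficient: adjusting for the T0 score would be worth about 20 participants per arm at the plan's assumed correlation, and 11 to 15 at higher values

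*Protocol article*

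**What the plan says.** Under Data Analysis Plan, Primary Noninferiority Analysis, the article draws its primary conclusion "using a modified noninferiority ANOVA of the T2 minus T0 change scores". The test is an F "statistic test jointly comparing the 4 randomization arms". Noninferiority is declared in either of two ways:
- the joint P value exceeds .15 and all three observed web-arm effects are −0.25 SD or better;
- the joint P value is .15 or less and all three one-sided 85% bounds lie above −0.35 SD.

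Effects are in units of the pooled baseline SD. No T0 covariate and no sex or cancer-type term is named.

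Under Study Arms, Overview: "Randomization is stratified by sex and cancer type using a permuted block design within strata for randomization".

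Under Sample Size Justification for Aim 1, "our power calculations assume change score SDs of 1", which "would be the case if the within-person correlation of measurement between periods is 0.5". The same paragraph adds: "If the correlation is of >0.5, as may likely be the case, the power will be better".

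Enrollment Goals sets the revised target at 60 per arm with both T0 and T2 data. Additional covariates appear only in secondary work: the 21st Century Cures Act period models and the moderator models. Neither adjusts the primary comparison for baseline.

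**The concern.** Every participant counted towards the target has a T0 score, and sex and cancer type are known at randomization. The primary model uses the T0 score only by subtracting it, which amounts to fixing its coefficient at 1. When the regression slope of T2 on T0 is below 1, subtraction over-corrects for baseline and adds noise that a fitted slope would remove.

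Two things are at stake. The first is precision, in a trial whose target fell from 140 to 60 per arm because of slow recruitment. The second is that the first branch of the rule compares observed point estimates with −0.25 SD. A chance difference in T0 means between arm A and the web arms shifts those estimates, and the planned model does not correct for it.

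**Working it through.** **Inputs from the article.** 60 per arm; T0–T2 correlation r = 0.5; SD 1 at both times, giving change-score SD 1; the two-branch rule; Table 5, rows unconditional on observed data.

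**Reproducing the plan.** The rule was simulated with 40,000 runs per scenario, bivariate normal scores, r = 0.5 and an arm-only change-score ANOVA:

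| Scenario, 60 per arm | Table 5 | Simulated |
|---|---|---|
| No effect | 79% | 79.4% |
| B and C at +0.2 | 86% | 86.0% |
| All web arms +0.1 | 92% | 91.6% |
| Heterogeneous | 71% | 70.8% |
| All −0.1 | 59% | 59.2% |
| All −0.2 | 36% | 35.3% |
| All −0.25 | 25% | 24.5% |
| All −0.3 | 16% | 16.1% |
| Only B at −0.35 | 23% | 23.4% |
| All −0.35 | 9% | 9.7% |
| Arm D very harmful | 2% | 1.9% |

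At 140 per arm the full rule gives 94.3%, against the stated 94%. The published figures therefore match an unadjusted change-score analysis.

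**Variance.** With SD 1 at both times:
- change score: 2(1 − r);
- ANCOVA residual: 1 − r²;
- ratio: (1 − r²) / [2(1 − r)] = (1 + r)/2.

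| r | Ratio | 60 per arm acts like | Gain per arm |
|---|---|---|---|
| 0.5 | 0.75 | 60/0.75 = 80 | 20 |
| 0.6 | 0.80 | 60/0.80 = 75 | 15 |
| 0.7 | 0.85 | 60/0.85 = 70.6 | 10.6 |

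With unequal SDs s₁ (T0) and s₂ (T2), change-score variance minus ANCOVA variance is s₁² + s₂² − 2r·s₁s₂ − s₂²(1 − r²) = (s₁ − r·s₂)². This is never negative, so the size of the gain depends on the equal-SD assumption but its direction does not.

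**The plan's rule with ANCOVA, 60 per arm.** Repeat simulations differ by up to about one percentage point.

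| Scenario | Change score | ANCOVA |
|---|---|---|
| No effect, r = 0.5 | 79% | 85% |
| No effect, r = 0.6 | 84% | 88% |
| No effect, r = 0.7 | 89% | 92% |
| All −0.35, r = 0.5 | about 9.5% | about 8% |
| Arm D very harmful, r = 0.5 | 1.9% | 1.0% |
| All −0.25, r = 0.5 | 24.5% | 24.4% |

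As a cross-check, a change-score ANOVA simulated at 80 per arm also gives 85% power under no effect.

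**Chance imbalance, r = 0.5.** If the arms differ by d at T0, the change-score contrast shifts by (1 − r)d in size. The standard error of arm A's T0 mean minus the web arms' average is √(1/60 + 1/180) = 0.149 SD. A difference beyond one standard error, in one direction or the other, arises in about one trial in three. With no true effect, change-score power is about 94% when arm A starts that much better and 56% to 58% when it starts that much worse; ANCOVA gives about 85% both ways. With all web arms at −0.35 and arm A starting better, false noninferiority is about 26% with change scores and 8% to 9% with ANCOVA.

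**Sex and cancer type.** The article gives no figure for how strongly these predict the outcomes, so their contribution cannot be computed. All of the gain above comes from the T0 covariate.

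**The case against.** The strongest reply is that nothing is stated wrongly. The primary outcome is defined as change from T0 to T2, a change-score ANOVA is unbiased under randomization, and the published power was calculated for exactly that test. This stands. A reader might infer that the planned test is biased or the stated power wrong, but the documents do not support that. The imbalance effect is conditional on the baselines that happen to occur and averages out over randomizations. Leaving out stratification factors errs on the conservative side.

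Second, the gain is modest against what was lost. The cut was 140 − 60 = 80 per arm, and 20/80 is a quarter. At r = 0.6 and 0.7 it is 15/80 = 19% and 10.6/80 = 13%, and the plan itself expects r above 0.5. This also stands: adjustment does not recover most of the lost precision.

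Third, changing the model now is not free. The Results section says data collection ended in September 2024 and analysis is under way. The sample-size section says the statistician and principal investigator were unblinded to a December 2023 conditional power calculation that used this rule. A new primary model would also no longer match Table 5. This limits how the change can be made, but it does not make the planned model efficient.

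Fourth, the covariates might be settled in an analysis plan not shown. That carries less weight here, because the article itself fixes the model, thresholds and standardization, and its power figures reproduce without adjustment.

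**Conclusion.** The point holds as one of efficiency. An arm-only change-score ANOVA gives up precision worth about 20 participants per arm at r = 0.5, 15 at r = 0.6 and 11 at r = 0.7, or roughly 6, 4 and 3 percentage points of no-effect power. It also leaves a rule based on point estimates exposed to chance baseline imbalance that is measured and could be corrected. The sizes assume 60 per arm, normal scores and equal SDs at T0 and T2.

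A reader might hope that adjustment would also control false noninferiority. It would not: with every web arm at −0.25 SD the rule still declares noninferiority about 24% of the time, and at −0.35 the improvement is only from about 9.5% to 8%. The operating characteristics of the rule are a separate matter.

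**What to change.** Analyse T2 (or T2 minus T0, which gives the same arm contrasts) by ANCOVA on arm, T0 score, sex and cancer type. Keep the contrasts against arm A in pooled baseline SD units and apply the existing thresholds to the adjusted estimates and bounds.

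Because data collection is complete and interim data were seen unblinded, make this a dated, openly reported amendment before any further comparison of outcomes by arm. State who had seen what, and report the planned change-score ANOVA alongside. If arm-level outcomes have already been analysed, leave the planned test as primary and report the ANCOVA as a sensitivity analysis.

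No new data are needed. The model uses at most five more degrees of freedom (one for T0, one for sex, three for the four cancer types) out of 240 − 4 = 236. The real cost is the amendment and restating the Table 5 probabilities for the adjusted model.
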